**Figure 1. F1:**
[figure not shown]
Overview of a typical single-case experimental design study flow.

SCED has been used in medical, psychological, and behavioral research for decades to better understand the mechanisms of intervention effects. Recently, it has also been used to assess the effectiveness of technology-based interventions in other areas [32], for example, in vulnerable populations such as adolescents experiencing psychological distress [33], individuals with serious mental illness [34,35], adults with severe autism spectrum disorder [36], and young children [37]. The extant literature suggests that SCED is a viable alternative to RCTs, especially for sensitive outcomes, because it allows for closer observation of individuals [38]—something which is critical for ensuring the immediate safety of participants living with IPV [26,27]. However, to the best of our knowledge, this will be the first adaptation of the methodology to IPV studies [32].

To gauge whether SCED is a viable approach for evaluating a web-based safety planning tool for English-speaking women in the GTA, we have established the following study objectives:

To understand whether women who are living with or have recently experienced IPV can be safely engaged for intense follow-up for the purpose of evaluating a safety planning interventionWe hypothesize that our safety protocols and individualized approach will allow for safe participation in the study, as measured by a lack of reportable or adverse events.To examine the preliminary effectiveness of WITHWomen Pathways and our novel safety protocols on 3 primary and 2 secondary outcomes of interestWe hypothesize that within-person changes to decisional conflict and depressive symptoms will show a decrease, whereas empowerment to take safety actions will demonstrate an increase.

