To quantify the pre-post changes in outcomes for each participant, we will follow the WWC guidance by calculating Tau-U, a nonparametric effect size metric. Tau-U allows for the estimation of intervention effects while accounting for trends that may be present during the baseline (preintervention) phase [53,54]. For each outcome and participant, we will compute (1) Tau (preintervention, A), to evaluate baseline trend; (2) unadjusted Tau-U (A vs postintervention, B), which compares data points between the baseline and postintervention phases without adjusting for baseline trend; and (3) adjusted Tau-U (A vs B), which corrects for any nonrandom trends in the baseline phase. Consistent with Fingerhut et al [54], our primary aim is not to assess statistical significance, which would be unreliable in small sample size designs such as SCED, but instead to interpret the direction and magnitude of observed effects. We will use previously validated benchmarks to classify effect sizes as small (0.20‐0.59), moderate (0.60‐0.79), or large (≥0.80) [53]. Even small effect sizes will be considered potentially meaningful when supported by consistent patterns observed through visual inspection of the data (see Table 2).

**Table 2. T2:** Five visual analysis measures of comparison typically used for single-case experimental design evaluation.

Measure	Definition
Nonoverlap of all pairs (NAP)	Values from baseline and intervention time points are paired, and a percentage of pairs whose values do not overlap is calculated.
Extended celeration line (ECL)	An NAP that controls for positive trends in the preintervention phase by calculating the proportion of postintervention data points that are above the median trend line plotted from preintervention data.
Improvement rate difference	It is calculated as the difference in the rates of increase in outcome variable data between the preintervention and postintervention phases by dividing the number of “improved data points” by the total number of data points in that phase.
Tau-U	Tau-U adjusted pairs each preintervention and postintervention observation to make n pairs. The number of positive-change, negative-change, and tied pairs is calculated for each outcome variable

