Percentage of nonoverlapping data, corrected (PNDC)	Particularly useful when anticipating an increase in the outcome variable postintervention, PNDC locates the highest data point in the preintervention phase and calculates the percentage of postintervention data points that exceed it. A data correction procedure is used to control for an upward preintervention trend.

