### Study Limitations

There are some notable limitations to this study. First, research activities require that women be able to speak and read English, which excludes non-English speakers and women with visual impairment. Second, with its multiple points of intervention and smaller sample size, SCED has safety and statistical limitations. First, having multiple contact points with each participant increases the chance that the abusive partner could become aware of her participation, increasing the risk of IPV. To address this, we have developed strict safety protocols and can promptly leverage our connections with local service providers should emergencies arise. SCED approaches also have multiple measurements in close temporal proximity, increasing participant burden. To help limit attrition, we will clearly communicate with potential participants about the time involved at the outset; invest in training for study team members to promote friendly, empathetic connection with participants; and provide fair compensation for the demands on participants’ time. Statistically, SCED carries four major risks: (1) the potential for a lack of variability in the preintervention and postintervention measures because measurements are completed at short intervals, (2) limited generalizability due to a small number of cases, (3) threats to internal validity due to test bias and social desirability bias [40], and (4) potential confounding effects due to the lack of randomization. To address risk 1, we will use the WWC recommendations for conducting sensitivity analyses and reporting multiple effect size estimators (eg, multiple visual analysis methods). Regarding risk 2, although multiple-case SCED (when rigorously evaluated) can be generalizable in many of the same ways as RCTs, this necessitates replication, which requires additional resources [57]. We do not anticipate this preliminary trial to be generalizable. Rather, it is intended to better identify the potential utility of SCED protocols in the evaluation of IPV-related interventions and adaptations that may be necessary. Regarding risk 3, we will use the percentage of nonoverlapping data, corrected (PNDC), to ascertain patterns of preintervention increase, as recommended by the WWC (see Table 2). Regarding risk 4, once this preliminary trial is complete, we intend to introduce randomization to different permutations of the WITHWomen Pathways app in future studies.

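### As worded in Table 2, PNDC and ECL credit only increases, although decisional conflict and depressive symptoms are hypothesised to fall

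*Protocol article*

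**What the plan says.** The study objectives at the end of the Introduction fix the expected directions: "within-person changes to decisional conflict and depressive symptoms will show a decrease, whereas empowerment to take safety actions will demonstrate an increase". Table 1 lists decisional conflict as primary and the PHQ-4 as secondary.

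Table 2 (Data Analysis Plan) describes five comparison measures. Two are worded for a rise only:

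- ECL is obtained by "calculating the proportion of postintervention data points that are above the median trend line plotted from preintervention data", and is said to control for positive baseline trends.
- PNDC is introduced as "Particularly useful when anticipating an increase in the outcome variable postintervention". The rule follows: "PNDC locates the highest data point in the preintervention phase and calculates the percentage of postintervention data points that exceed it". Its adjustment is also one-sided: "A data correction procedure is used to control for an upward preintervention trend".

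The Data Analysis Plan makes Tau-U the effect size for every outcome and participant. It treats small effects as potentially meaningful when visual inspection supports them, and cites Table 2 there. Study Limitations then promises several effect size estimators against low variability, and PNDC against test and social desirability bias, "to ascertain patterns of preintervention increase, as recommended by the WWC". Neither promise is limited to outcomes expected to rise. The article gives no reverse-scoring step and no mirrored rule.

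**The concern.** For a scale on which lower is better, both definitions count deterioration. A participant whose decisional conflict drops clearly and stays down would have a PNDC of about 0%, which anyone reading a nonoverlap percentage would take as no effect. A participant who worsens would score high.

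Three uses are affected. The Table 2 measures are cited as support for small Tau-U values, so a genuine small benefit on decisional conflict could look unsupported. They are the promised alternative estimators. And PNDC is the named guard against test and social desirability bias. On decisional conflict or the PHQ-4, the baseline drift that could imitate benefit is downward, and a check for baseline increase does not detect it.

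**Working it through.** The plan gives no figure for these measures, so there is none to reproduce. The Table 2 rules were applied as written.

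**Inputs from the protocol article.** 5 to 8 baseline points and a stability rule of at least 85% of points within 15% of the median (Preintervention Assessments); 8 later points (Postintervention Interviews).

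**Formulas.** A is baseline, B is postintervention.
- PNDC as worded = share of B above max(A); mirrored = share of B below min(A). The trend correction is left out because its formula is not given.
- ECL as worded = share of B above the extended baseline median line (split-middle line, or a flat median as a variant); mirrored = share below it.
- Tau = (positive pairs − negative pairs) / all A–B pairs.

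**Illustration 1, stable baseline (assumed values).** A = 60, 62, 58, 61, 59; B = 50, 48, 46, 45, 44, 42, 41, 40.
- PNDC as worded: max(A) = 62, so 0/8 = 0%. Mirrored: min(A) = 58, so 8/8 = 100%.
- ECL as worded 0%; mirrored 100%.
- Tau = (0 − 40)/40 = −1.00.

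The mirror-image rise scores 100%, 100% and +1.00 under the worded rules.

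**Illustration 2, falling baseline (assumed values).** A = 64, 62, 60, 58, 56; B = 52 at all 8 visits. The median is 60 and 15% of it is 9, so all five points lie within 51 to 69 and the stability rule is met. The split-middle line falls 2 per visit and extends to 54, 52, 50, …, 40.
- PNDC as worded 0/8 = 0%; mirrored 8/8 = 100%.
- ECL as worded: six points above, one tied, one below, so 6/8 = 75%. Mirrored: 1/8 = 12.5%.

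So ECL as worded can be high even though every later value is below every baseline value.

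**Simulation.** 10,000 series per setting. Assumptions: independent normal errors, SD 1, no trend, 8 later points. With 5 baseline points:

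| True fall | Mean PNDC, as worded | PNDC exactly 0% | Mean PNDC, mirrored | Mean ECL, as worded (split-middle) | ECL exactly 0% |
|---|---|---|---|---|---|
| 0.5 SD | 8.1% | 61% | 29% | 42% | 32% |
| 1 SD | 3.5% | 79% | 45% | 34% | 41% |
| 2 SD | 0.4% | 97% | 76% | 20% | 59% |
| 3 SD | 0.0% | 99.8% | 94% | 11% | 73% |

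Check: with no effect, a later point is the largest of six exchangeable values with probability 1/6 = 16.7%; the simulation gave 16.3%.

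With 8 baseline points, mean PNDC as worded is 4.8%, 1.9%, 0.2% and 0.0% for the same falls. With a flat median line and 5 baseline points, mean ECL as worded is 33%, 19%, 4% and 0.4%. With no effect ECL averages about 50%, so true benefit pushes it below its null value.

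**The case against.** The case for leaving the text alone has real substance.

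- **Table 2 is partly a glossary.** Its title presents measures in common use, and the PNDC entry says it suits an expected increase. That limits how much the table commits to. It still supplies no rule for an expected decrease, and Study Limitations then adopts PNDC without restriction.
- **Tau-U carries the main result.** It counts change in both directions and is read for direction and size. This stands: a fall appears as a negative value, and the scatterplots show it directly. A reader might infer that PNDC and ECL would contradict Tau-U. Strictly, a PNDC of 0% and a negative Tau-U both say the score did not rise. The harm lies in reading 0% nonoverlap as no benefit.
- **Baseline drift is handled elsewhere.** A reader might infer that downward drift goes uncorrected throughout. It does not: Tau on the baseline phase, adjusted Tau-U and the fitted baseline trend lines all address it. Only the PNDC safeguard misses it.
- **The count of outcomes.** A reader might add intimate partner violence and say three of five outcomes are affected. Preintervention Assessments says change in violence is not necessarily expected, so the conflict with stated hypotheses covers two outcomes.
- **Scoring direction is routine detail for a full analysis plan.** Silence would indeed be no finding. Here the article states a direction, and it is the wrong one for two hypothesised outcomes.

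**Conclusion.** The point holds for the supporting estimators. As worded, PNDC and ECL run against the hypothesised direction for one of three primary outcomes (decisional conflict) and one of two secondary outcomes (the PHQ-4, through depressive symptoms). For a clear fall PNDC is at or near 0%.

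The tempting stronger claim, that an effective intervention scores 0% on both measures, is not supported. PNDC exceeds 0% in 39% of simulated series at a 0.5 SD fall. ECL averages 34% at 1 SD and reaches 75% in the falling-baseline illustration.

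The percentages rest on independent normal errors, no baseline trend and no PNDC trend correction; the direction of the problem follows from the definitions alone. Severity is moderate: Tau-U is intact, and no decision rule or success threshold depends on PNDC or ECL.

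**What to change.** - Add the direction of benefit for each scale, for example as a column in Table 1.
- For the Decisional Conflict Scale and PHQ-4, either reverse-score before computing any nonoverlap measure, or define PNDC by the lowest baseline point with correction for a downward baseline trend, and ECL by points below the line. Treat the Composite Abuse Scale the same way, since lower is better there even though no change is predicted.
- Keep the current definitions for MOVERS and the safety strategies index.
- Word the PNDC check in Study Limitations as a check for baseline drift towards benefit.
- State one sign convention for Tau-U. Its benchmarks are given only as positive values, so say how they apply to a fall.
- Analysis is reported complete for 4 participants. State which direction was used for them, and recompute if needed.

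The cost is a few lines of text and a recode in the analysis program. No new data are needed and there is no real downside.

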### Handling Missing Data

SCED requires multiple data collection points with each participant, increasing the likelihood that one of these data collection opportunities will be missed. In the event of interim missing assessments (ie, a missed data point from an enrolled participant), we will still attempt to establish stability. To do so, we will leave a break in the time-series line for visual analysis; data points will not be connected across a missing observation. For the nonparametric effect size calculation (Tau-U), comparisons will be made using all available preintervention and postintervention data pairs, as the statistic does not require an uninterrupted series.

### Data Variability

To address potential variability in the data, our visual analysis will systematically examine the stability of data points within each phase, in addition to the level and trend. This will be supplemented by our calculation of SD for each outcome per participant in both preintervention and postintervention periods. This allows us to assess not only the occurrence of a change but also the consistency of the intervention’s effect, even with variable data in the preintervention or postintervention periods.

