The baseline interview is designed to last approximately 15 to 20 minutes and will end with a reminder that the participant will complete some of these same measures every 3 to 4 days for the next 2 to 3 weeks until stability is reached. Participants will receive CAD $10 (US $7.15) as an online gift card or through electronic money transfer upon finishing each preintervention interview. Following the established safety protocols for working with those experiencing IPV described above, preintervention baseline assessments can occur via telephone, in person, or via an online survey, using the mode that seems the safest for the participant [46]. For telephone-based assessments, we will also ask the participant before beginning each session if she is in a private space. Whether collected remotely or in person, the SCED data will be recorded via Zoho Survey (Zoho Corporation) and saved directly to a secure Zoho server.

After each participant’s fifth baseline interview, the research team will assess the overall score for each outcome measure. If the participant achieves stability, measured using previously cited criteria wherein at least 85% of preintervention data fall within a 15% range of the median for at least 1 primary outcome measure (Patient Health Questionnaire-4 [PHQ-4], Measure of Victim Empowerment Related to Safety [MOVERS], and Decisional Conflict Scale), they will progress to the intervention interview [47,48]. If stability is not reached after 5 assessments, baseline measurements will continue for 2 more weeks (3 additional baseline measures with CAD $10 (US $7.15) compensation at each assessment) and reassessed. If, at this point, the participant’s outcome measures are deemed stable, they will proceed to the intervention interview. If not, they will still advance to the intervention visit, but their data will not be included in the effectiveness evaluation. Using the standard SCED protocol, these assessments will result in at least 5 but no more than 8 baseline measurements, ensuring that every participant receives the intervention as soon as possible [49].

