### Data Analysis Plan

Following the SCED technical guidance published by the What Works Clearinghouse (WWC) of the US Department of Education’s Institute for Education Sciences [49], we will begin by computing descriptive statistics for each outcome measure, stratified by participant and intervention phase. For each scale, we will calculate the number of observations, mean, SD, SEM, minimum, and maximum, separately for the preintervention and postintervention periods. This will allow us to summarize overall patterns and assess changes in central tendency and variability over time.

The WWC also recommends visual inspection of data points and trend lines to gauge preintervention and postintervention effects [52]. To visualize the within-person patterns over time, we will create scatterplots for each participant and outcome measure, overlaying fitted linear trend lines for both the preintervention and postintervention phases. This will allow for visual inspection of potential shifts in level and trend following the intervention. A vertical reference line will denote the point of intervention onset.

Internal consistency will be assessed using Cronbach α, calculated on the basis of the preintervention responses for each scale described previously. These estimates will provide an indication of scale reliability prior to any intervention effects.

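### The before/after SD comparison is distorted on the three scales used to declare baseline stable, because the rule selects for low baseline spread; size unknown, minor

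*Protocol article*

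**What the plan says.** Two parts of the protocol article bear on this point.

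**How the SDs are used.** Data Analysis Plan computes n, mean, SD, SEM, minimum and maximum by participant and phase, and gives the purpose: "This will allow us to summarize overall patterns and assess changes in central tendency and variability over time". Data Variability has the visual analysis look at stability, level and trend within each phase, and adds: "This will be supplemented by our calculation of SD for each outcome per participant in both preintervention and postintervention periods". The stated benefit follows: "This allows us to assess not only the occurrence of a change but also the consistency of the intervention’s effect".

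**How the baseline is chosen.** Preintervention Assessments sets the first look: "After each participant’s fifth baseline interview, the research team will assess the overall score for each outcome measure". Stability means that "at least 85% of preintervention data fall within a 15% range of the median for at least 1 primary outcome measure", the listed scales being "Patient Health Questionnaire-4 [PHQ-4], Measure of Victim Empowerment Related to Safety [MOVERS], and Decisional Conflict Scale". The alternatives are an extension ("If stability is not reached after 5 assessments, baseline measurements will continue for 2 more weeks", which adds 3 measurements) and then exclusion: "If not, they will still advance to the intervention visit, but their data will not be included in the effectiveness evaluation".

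Postintervention Interviews fixes 8 assessments for everyone and attaches no stability condition. No section says that baseline SDs have been selected by the stability rule, or allows for it.

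**The concern.** The two SDs being set side by side are not obtained on equal terms. For at least one scale per included woman, the baseline series was accepted because its points happened to lie close together, whereas the postintervention series is taken as it comes. This is regression to the mean acting on spread. A baseline SD picked for being small is likely to be followed by a larger one, and on a scale that missed the criterion while another met it, a baseline SD picked for being large is likely to be followed by a smaller one. Neither movement needs an effect of the app.

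With 6 women planned and 4 completed, there is little room for such movements to average out. The plan also interprets direction, magnitude and pattern rather than statistical significance. A change in spread produced by the stability rule could therefore be taken for information about the app.

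**Working it through.** The article states no SD, CV or expected SD ratio, so there is no figure to reproduce. The check is a simulation of the plan's own rule with no effect of the app.

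**Inputs from the article**
- Criterion: at least 85% of points within the 15% range. At 5 points, 4/5 = 80% fails, so 5/5 is needed. At 8 points, 6/8 = 75% fails and 7/8 = 87.5% passes, so 7/8 is needed.
- Meeting it on any 1 of 3 scales is enough.
- Baseline length: 5, or 5 + 3 = 8. Women still unstable are excluded.
- Postintervention length: 8, without selection.

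**Assumptions not in the article**
- Scores are normal with constant mean and SD, and independent across visits and scales. Treating short questionnaire scores as continuous is an approximation.
- Within-person CV runs from 3% to 15%.
- The 15% range means ±15% of the median, or alternatively ±7.5%.

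**Method.** For 60,000 women per setting, draw 3 scales × 16 visits as 1 + CV × N(0,1). Apply the criterion at 5 visits, then at 8. For included women, compare the baseline sample SD with that of the next 8 visits.

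**Result, ±15% band: share of cases in which SD rises**

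| CV | Women included | Scale that met the rule | Scale that did not | All three, unsorted | No selection |
|---|---|---|---|---|---|
| 5% | 100% | 55% | rarely arises | 53% | 53% |
| 7.5% | 100% | 65% | 13% | 54% | 53% |
| 10% | 99% | 75% | 26% | 54% | 53% |
| 12.5% | 90% | 82% | 35% | 57% | 53% |
| 15% | 72% | 87% | 41% | 60% | 53% |

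The unselected 53% exceeds 50% only because 5 points are compared with 8. On the scale that met the rule, the post/pre ratio of mean SDs is 1.05, 1.18, 1.32 and 1.60 at CVs of 5%, 7.5%, 10% and 15%, against 1.03 without selection.

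**Arithmetic check on the unsorted column.** At a CV of 10%, about 58% of the gating scales of included women met the rule: 0.58 × 0.75 + 0.42 × 0.26 = 0.435 + 0.109 = 0.54. At 15%, about 41% met it: 0.41 × 0.87 + 0.59 × 0.41 = 0.357 + 0.242 = 0.60. The two opposite biases largely cancel in the aggregate, although not on any single scale.

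**Sensitivity**
- ±7.5% band: on the scale that met the rule, SD rises in 58%, 75%, 88% and 94% of cases at CVs of 3%, 5%, 7.5% and 10%. Unsorted, the figure at 10% is 64%.
- Lag-1 autocorrelation of 0.6, ±15% band: 71% at a CV of 10% and 83% at 15%, against 59% without selection.
- Scales correlated at 0.5, ±15% band: 74%, 82% and 87% at CVs of 10%, 12.5% and 15%.
- The fall on scales that failed the rule is less robust. It weakens as the CV grows, and with correlated scales and the ±7.5% band it disappears or slightly reverses at a CV of 10% or more.

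**The case against.** The strongest reply is that the article never sets up a formal SD comparison. The SD supplements visual analysis. There is no ratio, threshold or decision rule, and consistency of effect could simply mean scatter within the postintervention phase. That stands in part and limits the severity. It does not remove the point, because Data Analysis Plan names change in variability over time as a purpose of the phase summaries, and Data Variability ties the SDs of both phases to consistency of effect.

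A second reply is that scores 3 to 4 days apart may hardly vary. Study Limitations lists lack of variability as its first statistical risk. At a CV of 5% or less with a ±15% band the distortion is indeed negligible. But the plan also provides for extending baseline and excluding unstable women, so it allows that the criterion will bind for some.

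A third reply is that the output is by outcome and participant, not sorted by which scale met the rule. A reader might infer from the 75% to 87% figures that the planned tables will mostly show scatter rising. They would not: unsorted, the figure is 54% to 60% at the same CVs.

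A reader might also infer that the investigators will call a higher SD an inconsistent effect, call a lower one a steadying effect, or use the SDs to decide whether a small Tau-U matters. The article says none of this. Data Analysis Plan rests the Tau-U judgement on visual inspection, and Tau-U does not use the SD.

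**Conclusion.** The point holds in a limited form and is minor. On the scale by which a woman qualifies, the before/after SD contrast is biased towards a rise when the app has no effect, because one phase is selected for low spread and the other is not. The direction follows from the article's own rules, and no simulated setting gave a fall on that scale. It is a tendency, not a certainty for each woman.

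The size cannot be fixed from the article, which gives no within-person CV. With a ±15% band it runs from negligible at 5% to marked at 10% and above, and a ±7.5% reading of the band brings it in at smaller CVs. The opposite lean on scales that failed the rule holds at moderate CV only.

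The adapted Strategies Index and the Composite Abuse Scale are outside the stability rule and are not directly affected. No Tau-U value changes. What is affected is the meaning that can be given to a pre/post SD difference on PHQ-4, MOVERS and the Decisional Conflict Scale.

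**What to change.** In Data Analysis Plan and Data Variability:

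1. Keep the phase SDs as description.
2. Mark for each woman which scale or scales met the stability rule, and whether at 5 or 8 visits.
3. State that a pre/post SD difference on PHQ-4, MOVERS or the Decisional Conflict Scale is not evidence on the app's effect or its consistency.
4. Judge consistency from the scatter of the 8 postintervention scores about their own level or trend line.

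A simulated no-effect SD ratio is not a good benchmark here: it needs each woman's true CV, which the selected baseline cannot supply.

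The cost is a few sentences and one extra column. No new data, visits or participants are needed. The small downside is losing one descriptive contrast as evidence. Analysis of 4 women is complete, but recruitment continues and the article describes the results as still to be published, so the wording can still be applied to their interpretation.
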